## Abstract

**Introduction:**

The overall aim of the present project is to increase healthcare professionals’ ability to ask about exposure and to identify individuals exposed to intimate partner violence (IPV). The project will evaluate the effects of three different interventions that can be assumed to increase healthcare professionals’ ability to ask and identify individuals who have been or are exposed to IPV.

**Methods:**

This project has a quasi-experimental design. After a 2-month baseline period, participating care units (primary health centres, maternal health clinics and youth guidance clinics) will be assigned to one of three interventions to potentially increase the ability to enquire and identify patient exposure to IPV: (1) healthcare professionals’ use of a standardised questionnaire about exposure to IPV in patient meetings, (2) training through the use of a virtual patient case tailored to health professionals and (3) a combination of (1) and (2) earlier. Preintervention (baseline) and postintervention measurements of the health professionals’ enquiry and identification of patients exposed to IPV will be used to explore the effect of the interventions. Focus group interviews with the participating health professionals will be used as a qualitative method, applying thematic analysis, to explore which intervention they perceive as most effective in increasing their ability to identify victims of IPV.

**Analysis:**

Data analysis will focus on a comparison of pre- and post-measurements regarding the number of patients asked about and identified patients in each intervention arm that have been or are exposed to IPV. Measurements will be carried out per care unit at the group level. Qualitative data from focus group interviews will be analysed using thematic analysis.

**Ethics and dissemination:**

All participants will sign a written consent form and the study has been approved by the Swedish Ethical Review Authority (Dnr 2023-03399-01). The study will be conducted according to good clinical practice and the Declaration of Helsinki. The results of this study will increase knowledge about how identification of violence in close relationships can be improved in the clinical setting through publications in peer-reviewed journals and presentations at national and international scientific conferences.

**Study status:**

Recruiting since May 2024. Expected trial termination December 2026.

**Trial registration number:**

NCT06322251.

STRENGTHS AND LIMITATIONS OF THIS STUDYThe quasi-experimental design with pre- and post-measurements allows for assessments of changes over time and comparisons of different interventions, providing robust data on the effectiveness of each method.Our study fills a documented need to identify and evaluate useful and effective interventions that support clinical practice to identify exposure to intimate partner violence (IPV).The approach of using three distinct interventions (standardised questionnaire, training with virtual patients and a combination of both) is unique and allows for a comprehensive evaluation of how best to identify exposure to IPV.Our mixed-methods approach, combining quantitative data and qualitative insights from focus group interviews analysed using thematic analysis, provides a richer, more nuanced understanding of the interventions’ feasibility and their impact.The study will be conducted within specific healthcare settings in the Stockholm region, Sweden, which may limit the generalisability of the results to other regions or healthcare systems.

## Introduction

 Intimate partner violence (IPV) is widely recognised as a significant public health concern, with profound implications for affected individuals. Globally, nearly one-third of women have experienced IPV during their lifetime.^1^ The WHO defines IPV as ‘any behavior within an intimate relationship causing physical, sexual, or psychological harm, encompassing physical aggression, sexual coercion, psychological abuse, and controlling behaviors’.^2^ Most IPV incidents are directed towards women by male partners.^3^

### Psychological and physical sequelae of IPV

Extensive research from diverse cultural contexts has documented the multifaceted consequences of IPV exposure on the health of women. These consequences include chronic pain, functional gastrointestinal disorders, gynaecological problems, depression and anxiety symptoms and post-traumatic stress disorder.^4^,^9^ Notably, recent studies have shed light on the insidious nature of psychological IPV and its severe adverse health effects.^10^,^14^ Women who have experienced IPV often present to healthcare facilities and seek assistance for various and diffuse symptoms. The root cause of their health problems is often related to exposure to IPV, but this frequently goes undisclosed.^15 16^

### Screening of IPV

Many healthcare providers find it difficult and challenging to ask their patients or clients about potential IPV exposure, and in the case of a positive answer, they often do not know how to guide and help the client.^3 17 18^

Thus, despite the relatively high prevalence and adverse effects of IPV, IPV exposure tends to go unnoticed during healthcare visits. Consequently, timely interventions and support for affected women are hindered.^15 16^ Within healthcare settings, standardised questionnaires aimed at eliciting information about IPV exposure have been developed.^19^,^21^ However, there is ongoing debate regarding the effectiveness of universal screening for IPV. While the WHO^22^ clearly advises against routine enquiry in all healthcare encounters, international meta-analyses suggest that systematically asking patients about IPV, when assessing health conditions that are possibly linked to or complicated by IPV, can significantly increase the identification of victims.^17 18^ In the Swedish setting, it is not yet known whether the use of IPV questionnaires—an opportunity to ask patients/clients directly about potential IPV exposure—can be a helpful tool for healthcare professionals.

### Virtual patients

Despite the increasing demand for digital education solutions, studies exploring the use of virtual patients (VPs) in a primary care context in connection with IPV are lacking, presenting an opportunity for further investigation. VPs represent simulations of clinical scenarios with digital patient encounters. They can be used to train clinical reasoning and assessment, making them a valuable tool for healthcare professionals. VPs facilitate active learning and problem-solving while providing automatic feedback on patient management.^17^,^23^ Simulations with VPs are designed around problem-centred scenarios, engaging users in solving real-world-like problems. VPs may incorporate interactive features encompassing medical history taking, physical examination, laboratory tests and diagnostic and treatment plans.^24^ This approach not only activates long-term memory but also prompts the application of previous knowledge to generate new insights^25^ thereby potentially contributing to improved clinical reasoning and knowledge acquisition.^25 26^ VPs have been successfully used as a training arena based on other issues, including traumatised refugees.^26^ It is therefore useful to study whether VPs can also be used to train professionals to discover and manage IPV.

To summarise, the high incidence of psychosocial and physical health problems among people exposed to IPV may be associated with presentations at health services. Given the high prevalence of IPV and the associated medical consequences and costs, it is critical to address this public health problem. Our goal is to contribute tools to ask about and identify more individuals exposed to IPV.

## Objectives

The *overall aim* of this project is to increase primary care professionals’ ability to identify patients exposed to IPV. The *specific research questions* are: (1) to what extent do the following three interventions contribute to asking about and identifying potential victims of IPV: (a) the use of a standardised questionnaire to screen for exposure to IPV, (b) healthcare professionals’ training in IPV, using VPs tailored for clinical use and (c) a combination of interventions (a) and (b) earlier and (2) which of the three interventions do healthcare professionals experience as most effective to increase their ability to enquire about and identify and respond to victims of IPV?

## Methods and analysis

### Study design

This study has a quasi-experimental design. After a baseline period, three interventions will be compared with evaluate their effects on healthcare professionals’ ability to ask and identify patients who are exposed to IPV. Three different types of care units will be included. These care units are primary health centres, maternal health clinics and youth guidance clinics, which will be assigned to deliver one of three interventions: (1) use of a standardised questionnaire for patients, (2) training using VPs tailored for healthcare professionals and (3) a combination of (1) and (2) above. Pre- and post-measurements of the health professionals’ identification of patients exposed to IPV will be used to explore the effect of the interventions. The focus group interviews with the healthcare professionals will be conducted as part of a qualitative methodological approach to complement the quantitative data. The trial is registered at ClinicalTrials.gov (NCT06322251). An overview of the design and interventions is shown in figure 1.

**Figure 1 F1:**
[figure not shown]
Overview of study design including the three interventions *standardised questionnaire*, *virtual patient* and *combination of the two*, as well as study settings. Preintervention and postintervention measurements of the number of identified patients exposed to IPV will be carried out at all study sites. IPV, intimate partner violence.

### Setting

The choice of healthcare units is based on the Swedish National Board of Health and Welfare’s mapping of important care units for identifying IPV.^27^ Accordingly, we will recruit health centres, maternal health clinics and youth guidance centres. *Health clinics* are primary healthcare facilities that provide a wide range of medical services to the public. These clinics serve as the first point of contact within the Swedish healthcare system and play a crucial role in maintaining public health. *Maternal health clinics*, also known as midwifery clinics, are specialised healthcare facilities that provide a wide range of services related to pregnancy, childbirth and postnatal care. These clinics are an essential part of Sweden’s healthcare system, ensuring the well-being of mothers and babies. *Youth guidance centres* are facilities that provide support and services specifically for young people, typically aged 13–25 years. These centres offer a wide range of services aimed at addressing young people’s health and well-being, including physical, mental and sexual health. There is no formal minimum age for patient inclusion in this study. In Sweden, youth guidance clinics routinely offer services to individuals from the age of 13, and it is standard practice to ask about exposure to violence in this age group. In our study, data from youth clinics will be collected through anonymised registry data, and according to the Swedish Ethical Review Authority, these individuals are therefore not considered study participants in the formal sense. While there are currently no standardised routines or structured questions for asking about IPV in this age group, our intervention aims to support and improve this practice.

### Population

#### Recruitment

The recruitment process differed for the three types of facilities, due to their number and size:

*Health centres* were informed about the study and invited to participate. As of January 2024, there were 235 healthcare units in Stockholm region. The inclusion process had two steps:

Provider: units were included if they were run by the Stockholm County Health Department.Size: units with more than 8500 listed patients were included.

This resulted in 41 eligible units. In the second step, these units were ranked using a socioeconomic Care Need Index (CNI) to ensure diverse representation.This index, based on variables such as employment status, education level, age, single parenting and country of birth, was used. Invitations were sent to every second and third unit on the list (28 units in total), starting with the lowest socioeconomic index. Six health centres agreed to participate, and healthcare professionals consisted of general practitioners (GPs), district nurses and nurses.

*Maternal health clinics* were informed about the study and invited to participate. As of January 2024, there were 70 maternal health clinics in Stockholm region, and all were invited. Ten clinics agreed to participate, with midwives as the primary professionals.

*Youth guidance clinics* were informed about the study and invited to participate. As of January 2024, there were 29 youth guidance clinics in Region Stockholm, and all were invited. 11 clinics agreed to participate, with midwives as the primary professionals. Of note, there is no overlap in midwives’ employment at the maternal health and youth clinics.

### Procedures

#### Baseline assessments

Consenting healthcare professionals will receive information about the study. During a 2-month study period, baseline measurements will be performed.

The quasi-experimental design is based on pre- and post-measurements to assess the proportion of patients asked about possible exposure to IPV and identify persons exposed to IPV. Baseline measurement will be recorded (before randomisation to intervention) by all participating clinics over a 2-month period regarding how many patients they identify who have been exposed to IPV.

In terms of the *health clinics* and *youth guidance clinics*, data regarding the number of patients asked about IPV and the number of patients exposed to IPV will be retrieved from the medical record system Take Care, in which healthcare professionals document whether they have asked the patient about exposure to violence and what the patient has responded. This will be carried out by healthcare professionals as part of their regular documentation of the patient’s medical visit. Information about measures taken and the support given by the healthcare professional if the patient reports exposure will also be documented and retrieved from the same medical system.

Notably, in relation to *maternity clinics*, there are no diagnostic codes for exposure to IPV, and this information cannot thus be searched for in patients’ medical records. The research group has therefore developed a simple protocol in which healthcare professionals can record statistics on how many patients have been asked about possible exposure to IPV and how many patients have disclosed exposure to IPV during the study period.

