### Outcome measures

*Primary outcome:* the primary outcome is the number of patients asked about IPV and patients identified exposed to IPV. This will be investigated before (baseline) and after the intervention period. Data will be measured at group level within all participating healthcare units (healthcare centres, maternal health centres and youth guidance clinics). Measurements will take place per care unit (at group level), and the analyses will mainly be comparisons of pre- and post-measurements.

The estimated number of patient visits reflects the total volume at participating units during the study period. The study does not analyse individual patient data beyond whether IPV was asked about and disclosed. Each unit will include its usual patient population, meaning youth guidance clinics will include adolescents, including those under 18 years of age. Screening will be conducted according to local protocols and ethical approval requirements.

It is important to note that the lifetime prevalence of IPV, often reported in global estimates, differs substantially from past-year prevalence. In this study, the screening tool focuses on exposure within the past 12 months, as this timeframe is most relevant for identifying individuals currently at risk and in need of clinical intervention. Consequently, the number of cases detected through screening will be lower than lifetime prevalence figures.

As specified in the research questions, the aim of this study is to evaluate interventions that improve healthcare professionals’ ability to ask about IPV and identify exposed individuals. The study does not analyse health outcomes or long-term health effects of IPV. The standardised questionnaire described is used solely as part of the intervention to facilitate enquiry and identification, not for collecting or analysing clinical health data. The primary outcome is limited to the number of patients asked about IPV and the number of patients who disclose exposure during the study period.

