*Sample size calculation:* at the health centres, the healthcare professionals are particularly represented through GPs and district nurses. At the maternal health centres and youth guidance clinics, midwives are the main profession represented. We estimate that approximately 60 healthcare professionals will take part in each intervention arm (figure 1). GPs and midwives meet approximately seven to ten patients per day, a number that may vary depending on healthcare professionals working full- or part-time. However, we estimate that there is a sufficiently large base for a quasi-experimental design (ie, a preintervention and postintervention measurement with comparisons between the interventions), where the main outcome measures are the number of asked and identified persons exposed to IPV. Thus, approximately 6000 patients will be approached in each intervention arm during the study period. With a reported national prevalence of IPV of 7%, 420 cases of IPV could potentially be identified in every study arm. It should be noted that the 7% prevalence of IPV is based on a national sample and may vary in the study setting. These numbers are estimated to be large enough to detect a medium effect size with a power of 0.80 and an α-level of 0.05.

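### The denominator for the logistic regression is never stated, and the maternity form as described (10 of 27 clinics) supplies none for the 'asked' outcome

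*Protocol article*

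**What the plan says.** The outcome is described in two ways. Outcome measures in the Protocol article states that "the primary outcome is the number of patients asked about IPV and patients identified exposed to IPV". Baseline assessments says the pre- and post-measurements serve "to assess the proportion of patients asked about possible exposure to IPV".

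Quantitative analysis then plans logistic regression with *asked* and *identified* as outcomes and with time, arm and their interaction as predictors. Data are to be analysed within each study setting. No denominator is given for either outcome.

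The data sources differ by setting:

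- **Health and youth clinics.** Baseline assessments says that "data regarding the number of patients asked about IPV and the number of patients exposed to IPV will be retrieved from the medical record system". The system is Take Care, where staff document whether they asked and what the patient answered.
- **Maternity clinics.** The same section says that "there are no diagnostic codes for exposure to IPV, and this information cannot thus be searched for in patients’ medical records". A simple form was therefore developed, on which staff "record statistics on how many patients have been asked about possible exposure to IPV and how many patients have disclosed exposure to IPV".

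The only reference to total volume is in Outcome measures: "The estimated number of patient visits reflects the total volume at participating units during the study period". It is an estimate, it counts visits, and it is not linked to the regression.

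**The concern.** A logistic regression of *asked* needs patients who were asked and patients who were not. Every patient counted on the maternity form as described was asked, so the outcome does not vary. Because the analysis is done within each setting, the other two settings cannot supply the missing patients.

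A model of *identified* can be fitted to the form's two counts only by using those asked as the base. That base is itself affected by treatment. The Interventions section tells questionnaire users to ask at all visits, with some exceptions, and gives no such instruction for virtual-patient training alone. Who is asked may therefore differ by arm and period, and the time-by-arm term would compare differently selected groups.

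At stake is whether the primary analysis can be carried out as planned in one of the three settings, and whether *identified* means the same thing in all of them.

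**Working it through.** **1. The plan's own figure.** The sample size paragraph gives about 6000 patients approached per arm and a prevalence of 7%: 6000 × 0.07 = 420, as stated. The base there is patients approached, which differs from both a number and a proportion of patients seen. The paragraph also says "We estimate that approximately 60 healthcare professionals will take part in each intervention arm", each seeing 7 to 10 patients a day. Then 6000 / 60 = 100 patients per professional, or 100/10 = 10 to 100/7 = 14.3 full working days. The article does not say how patients approached relate to patients seen over a two-month period, and it notes that part-time work varies. This figure therefore does not settle the denominator.

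**2. Share of clinics.** Recruitment lists 6 health centres, 10 maternity clinics and 11 youth clinics: 6 + 10 + 11 = 27, and 10/27 = 37.0%.

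**3. What each model needs.** For one clinic and period, let N be patients seen, A patients asked and D patients disclosing. The form as described gives A and D.

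- *Asked*: odds = A / (N − A). Needs N, which is not on the form.
- *Identified* among seen: odds = D / (N − D). Needs N, which is not on the form.
- *Identified* among asked: odds = D / (A − D). Computable, but a different estimand.

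**4. How much depends on N.** The counts here are assumed, because the article gives none: before, N = 1000, A = 300, D = 15; after, A = 600, D = 36, with N varied. Each entry is the odds after divided by the odds before.

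| N after | *Asked* | *Identified* among seen | *Identified* among asked |
|---|---|---|---|
| 800 | 7.0 | 3.09 | 1.21 |
| 1000 | 3.5 | 2.45 | 1.21 |
| 1500 | 1.56 | 1.61 | 1.21 |
| 2000 | 1.0 | 1.20 | 1.21 |

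For example, with N = 1000 after, *asked* is (600/400) / (300/700) = 3.5. Among those asked, the ratio is (36/564) / (15/285) = 1.21 in every row.

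The same two recorded counts are thus compatible with no change in asking or with a sevenfold rise in its odds. The range of N was chosen to show the dependence and is not a forecast for these clinics.

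**The case against.** The strongest reply is that nothing is lost. The reason given for the form is that IPV information cannot be searched for in maternity records; nothing is said against counting patients or visits. A reader might infer that 37% of clinics have no usable denominator at all. The documents do not support that: totals may be held in booking data, and disclosure among those asked can be computed from the form.

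Maternity clinics are also not alone. For the other 17 clinics the article likewise names only asked and exposed counts, although a patients-seen count is plausible there because the source is the visit record. And this is a journal article: the form's full field list and the regression denominator may stand in a document not shown.

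These points limit the finding but do not remove it. The form is described by what it records, and a later analysis plan can define a denominator but cannot create a count that was neither collected nor extracted.

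Another reply is that the outcome is a count, so no denominator is needed. If arms run concurrently, a proportional change in volume common to them would largely cancel in the comparison between randomised arms. It would not cancel in the within-arm pre/post comparisons, which Outcome measures describes as the main analyses. In any case, the model named is logistic regression, not a count model.

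A reader might also infer that the results would reverse sign, or be diluted by staff who do not take part. The article does not make identified-per-asked its analysis, and it gives no asking rates, yields or share of non-participating staff. Neither effect can be sized from it.

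**Conclusion.** The point holds in a limited form. The article describes one outcome as both a number and a proportion and analyses it by logistic regression without stating a denominator. In 10 of 27 clinics (37%), the form as described cannot support the model for *asked*, nor one for *identified* among all patients seen. What it does support, disclosure among those asked, is conditional on the target of the interventions.

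This rests on reading the form as holding only the two counts named, and on analysis within setting as stated. It does not show that patient totals are unobtainable. The odds ratios in the working rest on assumed counts and show dependence only. Recruitment has run since May 2024, so some baseline periods may already be complete, which makes it more pressing to secure the totals.

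**What to change.** Add to the maternity form, or extract from booking data, the number of unique patients seen (or eligible, given the stated exceptions to asking) per clinic in each measurement period. If booking data hold this, it can be done retrospectively for periods already completed. Obtain the same count from Take Care for health and youth clinics.

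Use it as the common denominator in every setting, arm and period: proportion asked = asked / seen, and proportion identified = identified / seen. Disclosure among those asked can be reported as a secondary description. Ideally, restrict all counts to patients of participating professionals; this is desirable but less well supported by the text than the count itself.

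Then make Baseline assessments, Outcome measures and Quantitative analysis say the same thing. The cost is one extra count on a form, or one extra query per data source, and a few sentences of text.
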